***Post-release visit:***

After learning about a participant’s release, study staff will contact the study participant using previously collected locator information to confirm or arrange for a post-release visit within 14 days after release. For community-recruited individuals, this visit will take place during the initial baseline visit when possible. An appointment will be made for the participant to meet with study staff at designated, private space (e.g., at local CBOs or GW research clinic space). At this time, the study team will update the participant’s locator information, provide a resource/referral list for medical services, and provide a $50 incentive for their time. The payment is in the form of an American Express Gift Cheque. For those in the intervention arm, study staff will provide a cell phone and training on the text messaging portion of the intervention (described below). All study participants will be reminded about the monthly check-in calls and the 12-week and 24 week visits, and an appointment will be made for their next study visit. A blood draw will be conducted to provide a baseline measurement of plasma viral load and CD4 count (see 12-week/24-week study visit section for description about blood draw).

**Intervention arm:** Participants randomized to the intervention arm will receive a cell phone/SMS texting intervention that will begin at baseline visit 3. This intervention will consist of using cell phone-delivered automated SMS text-messaging with the intent of improving linkage to community HIV care and adherence to ART (if prescribed); and reinforcing the prevention plan from the CARE+ Corrections session completed in jail prior to release. In addition to SMS text-messaging, the cell phones will provide participants with a method for contacting their HIV clinic and other services providers (AIDS service organization case manager, social workers, re-entry service providers, etc.).

The study will provide basic cell phones and pre-paid cell phone plans to study participants who do not possess a cell phone at the time of the post-release visit. For participants who do own a cell phone with text messaging capability, participants will have the option of using their own cell phones and the study will provide a standardized monetary reimbursement for the costs incurred through study activities. Participants who possess a cell phone that does not have text-messaging capability will be provided a study phone.

Provision of cell-phones: Participants who do not possess a cell-phone will be provided with a Droid 4 Prepaid Phone ($49.99), or similar phone, with an unlimited text bundle and 400 minute calling plan or similar plan (~$40/month). The cost of the phone, the initial activation fee and costs for the unlimited text and calling minutes bundle will be covered by the study. Study staff will pre-purchase the cell phones and cell phone plans. All cell phone bills will be sent directly to study staff. The text-messaging and calling plans will be renewed on a monthly basis during the study follow-up period of 24 weeks. At the completion of the follow-up period, cell phone plans will be cancelled.

Use of existing cell phone: Participants who possess a cell-phone with text-messaging capability at the time of the post-release/follow-up study visit will have the option of using their own phone to receive the SMS text-messaging intervention and to use for communication with their community providers. Participants using their own cell-phones will be asked to provide information regarding their cell phone make/model, cell phone number, and cell phone provider/plan (including text messaging and call plans). Participants who use their existing phone will be reimbursed a standardized monetary amount per month based upon the anticipated cost related to receiving study text messages delivered through the intervention, plus reimbursement for an estimated volume of calls between the participant, study staff, and community providers. Reimbursement will accrue on a monthly basis and participants will collect this reimbursement at the 12 and 24 week study visits or have the option of picking it up on a monthly basis at the GWU community research site.

Training on cell-phone intervention: All participants will receive training delivered by study staff on the cell phone intervention. This will include training on the use of the cell phone as well as how to view and respond to text messages. The staff member and the participant will practice sending and viewing text messages to confirm that the participant understands how to use the phone and text messaging. The staff member will review the text-messaging plans and the use of customized messages (as described below). To facilitate cell phone communication with community providers, the staff member will assist the participant with programming important phone numbers into the cell-phone for easy retrieval and use. Phone numbers will be obtained from the DC Ex-Offenders Returning Citizens Referral List (see Appendix M) and will include phone numbers for medical providers, community-based organizations, re-entry services, etc. The staff member will also review the lost cell phone policy (described below).

Cell-phone/SMS text messaging intervention content: Separate text messaging content will be used for linkage to care, ART adherence, and the promotion of the CARE+ Corrections prevention plan. Text-messages will be delivered through a contracted SMS provider. Participants will be asked to send a response to the text message within 24 hours when a study text message is received. For each content category, the participant will choose from pre-scripted messages or, if technically feasible, the participant will have the option of creating a customized message as described below. In addition, for each content category, the participant will be able to choose from several different text-message frequency options (such as daily, every other day, three times weekly, weekly). The frequency of text messages in each content category can subsequently be changed by the participant at the monthly check-ins according to preference. To maintain confidentiality, text messages will not contain participant names, mention of HIV infection or HIV medications, or specific providers that only provide HIV care.

Linkage to care content: Text messages will be sent to remind the participant about his/her upcoming HIV appointment in the community. In addition, the message will ask the participant to contact their provider if s/he anticipates difficulty in attending the scheduled appointment. We will ascertain the participant’s next appointment during the monthly check-in phone call in order to set up or adjust the reminder text message. The participant will choose from pre-scripted appointment reminders or, if technically feasible, will create a customized message. The linkage message chosen by the participant will be recorded by the staff member.

- Pre-scripted text message example: “Don’t forget your upcoming Unity appointment. Call the clinic at 202-XXX-XXXX if you can’t make it”.
- Customized text message example: “Don’t forget your upcoming meeting at Church. Call the pastor if you can’t make it”.

Message reminders will be sent out at pre-determined intervals (e.g., weekly in the month before the appointment and then more frequently during the week of the appointment). Changes to text message content (pre-scripted or customized) will be recorded by the RA and will be entered into the SMS database.

A query message will be sent the day after the scheduled appointment and will ask “How did your appointment go? If OK, reply 1. If not OK, reply 2.” If the participant replies “1”, no further action will be taken. If the participant replies “2”, or if the participant does not respond to the query message within 24 hours, a study staff member will call the participant on their cell phone to assess barriers to care and the staff member will provide referral information (clinic, social work, case management) as needed. Responses to these texts and action taken by study staff will be recorded by the RA and then entered into the SMS database.

Adherence to ART content: For participants prescribed ART at the time of the baseline visit 3, text message reminders will be sent to remind the participant to take his/her ART. The participant will choose from pre-scripted ART medication reminders or, if technically feasible, will create a customized message. The ART adherence message chosen by the participant will be recorded by the staff member.

- Pre-scripted text message example: “Don’t forget your medications today. They are important!”
- Customized text message example: “Don’t forget to eat skittles today. They are important!”

Participants will select from different frequency options for ART medication reminders. The preferred frequency will be recorded and will be entered into the SMS database. Participants will have the option of changing this frequency at the monthly check-in call. Changes to text message frequency will be recorded by the RA and will be entered into the SMS database. Participants in the intervention arm who are not prescribed ART at the time of the baseline visit 3 will be asked at the monthly check-in calls if ART has been started. For participants who start ART during the follow-up period, they will have the option of adding ART reminders to their ongoing intervention according to the procedures described above.

CARE+ Corrections prevention plan content: During the CARE+ Corrections session completed in jail, participants will receive counseling in a number of areas including: post-release linkage to HIV care; post-release ART adherence; sexual risk reduction counseling; substance use risk reduction counseling; and working with your HIV provider. At the baseline visit 3, a staff member will review the individual prevention plan created during the CARE+ Corrections session with the participant and the participant will decide upon a prevention message to be used in the text-messaging intervention. The participant will choose from pre-scripted prevention messages created from the CARE+ Corrections content or, if technically feasible, will create a customized message. The prevention message chosen by the participant will be recorded by the staff member.

- Pre-scripted text message examples:
  - “Don’t forget to use protection. Protect yourself and your partner!”
  - “Don’t forget to meet with your case manager. She can help!”
  - “Watch out for partying. It can make you lose focus!”
- Customized text message examples:
  - “Stay away from drinking alcohol. Makes you forget your meds”
  - “ Call your sponsor, she can help you stay on track”
  - “Talk to your partner about staying safe. That’s important for both of you”

Participants will select from different frequency options for the CARE+ Corrections counseling reminders. The preferred frequency will be recorded and will be entered into the SMS database. Participants will have the option of changing this frequency at the monthly check-in call. Changes to text message frequency will be recorded by the RA and will be entered into the SMS database.

Barriers to community care content: The CARE+ Corrections session will also identify potential barriers to community care. The participant will choose from pre-scripted prevention messages created from the CARE+ Corrections content or, if technically feasible, will create a customized message. The prevention message chosen by the participant will be recorded by the staff member.

- Pre-scripted text message examples:
- “Get your benefits/insurance programs set up: call xxx-xxx-xxxx”
- Customized text message examples:
  - “Don’t forget to sign up for that program: call xxx-xxx-xxxx”

This message will be delivered once weekly to participants during the time period between the start of the SMS intervention and the first monthly check-in (approximately 4 weeks). If a participant is re-incarcerated and released during the study follow-up period, this content area will be repeated during the 4 weeks after release.

Administrative messages to all participants:

- A welcome message during the first week after registration
- Messages reminding participants about their monthly check-in with study staff

Tracking of text messages: For each participant, a staff member will record the message reminders selected for each content category and these will be entered into the SMS database. Text messages will be automatically delivered according to the scheduled frequency. For each participant, the SMS contractor will track messages sent and received by the participant and responses sent by participant back to study staff.

Lost cell-phone policy: If a participant who receives a study phone loses the phone, one replacement cell phone/plan will be provided per participant during the 24 week follow-up period. The cell phone plan of the original phone will be terminated immediately upon learning that the phone was lost. If the second phone is lost during the follow-up period, the cell phone plan will be terminated immediately upon learning that the phone was lost and no further phones will be provided to the participant.

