**Specific aim:**

This study will investigate whether an intervention (CARE+ Corrections) delivered to HIV-infected detainees within the DC Department of Corrections (both the Central Detention Facility and the Central Treatment Facility (CTF)) and recently-released ex-detainees in the community can improve linkage to community HIV care and adherence to HIV medications after release. The intervention is modeled after **CARE**, which is a technology based HIV-counseling tool used in other settings. We have adapted CARE to create **CARE+ Corrections**, a tool designed specifically for incarcerated and recently-released populations. Counseling via CARE+ Corrections will be delivered pre-release or within 6 months after release and will consist of a one-time computerized counseling session delivered by a tablet computer that will provide interactive counseling related to risk behaviors, linkage to community HIV care, and HIV medication adherence. This counseling session will be approximately 30-40 minutes in length and will be conducted within the DOC facilities or in a community setting. CARE+ Corrections will be coupled with a cell phone/text messaging intervention that will be delivered in the community, after release from a correctional facility. The cell phone/text messaging intervention will consist of participants receiving a cell phone, or use of an existing personal cell phone, that the study team will use to deliver reminders about HIV medical appointments and taking HIV medications. The study is a randomized controlled trial where one-half of the participants will receive the intervention (CARE+ Corrections plus the community-based cell phone/text messaging intervention) either inside the correctional facility, in addition to standard discharge planning services, or in the community right after release. The other one-half of study participants will view an educational video related to the prevention of overdose following release from the correctional facility, in addition to standard discharge planning services, or in the community right after release. We will follow all participants for 6 months after release/study entry during which we will conduct follow-up assessments at 12 week and 24 week appointments to determine if the linkage to care and adherence to HIV medications were higher in the intervention arm.

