***Baseline visit 1:***

- Within 1 week of the screening and enrollment visit, all study participants will return to complete a baseline assessment via computer-assisted personal interview (CAPI) (See Appendix E).

- An RA will assist with the administration of the CAPI. This will be conducted in a pre-designated space that affords confidentiality. The CAPI will be interviewer-administered by the RA who will set up the computer, ask questions to the participant and record the responses in the laptop/tablet. Participants recruited inside the DC DOC facilities will complete the “DOC Baseline CAPI” (lasting approximately 30 to 40 minutes) inside the DOC and the “Community Baseline CAPI” (lasting approximately 20-30 minutes) at the post-release visit. Participants recruited in the community will complete the “Combined Baseline CAPI” (lasting approximately 50-60 min) at enrollment.

.

- The CAPI will assess the following domains (see Appendix E for full CAPI content):
- Demographics
- Service Utilization
- Access to Care
- Mental Health
- Sexual Risk Behaviors
- Substance Use
- HCV/HBV/STI/HIV Testing & Treatment
- HIV Medication Adherence
- Post-Release Contact with HIV Healthcare Provider
- Criminal Justice
- Post-Release Concerns

Note: The baseline assessment may occur during the screening, consenting, and enrollment visit, as determined by the facility. In addition, due to operational time constraints in the facility, some of these sections may be administered during the post-release community visit.

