***Baseline visit 2:***

Within 1 week of baseline visit 1, participants will complete baseline visit 2, which includes random assignment to the study arm, updates to the study locator information, and medical chart review. Depending on the operational time constraints in the facility and in the community GWU research space (some of which is rented from local CBOs), baseline visit 2 may occur immediately after the screening, consenting, and enrollment process, as determined by the facility or depending on time constraints at the GWU research clinic space.

For participants recruited in the community, a blood draw will be conducted to provide a baseline measurement of plasma viral load and CD4 cell count (baseline only) (see 12-week/24-week study visit section for description about blood draw). Study participants will be randomized at this point to either the 1) intervention arm or 2) the control arm. A 1:1 block randomization scheme will be created using a SAS program to select random assignments. Blocks of 4 will be used to ensure equal population of each group during the course of the study. The study coordinator will manage the randomization list. Prior to the visit, the RA will consult with the study coordinator for the randomized assignments. At the beginning of this visit with the participant, the RA will administer either the intervention (CARE+ Corrections tool) or the control condition to the participant based on their assignment.

- Intervention Arm:

Participants will complete the CARE+ Corrections counseling session, which will last less than 30 minutes. The CARE+ Corrections session will consist of the following:

- The CARE+ Corrections tool is a computerized, one-session motivational interview (for an outline of the CARE+ Corrections tool, see Appendix F: CARE+ Corrections Flow Chart and Excel Spreadsheet).

- The CARE+ Corrections session will be conducted using a laptop computer or tablet with a touch screen and consists of an audio-assisted session in which participants provide responses to questions about demographic characteristics, sexual risk behaviors and attitudes, substance use, mental health, and HIV treatment and adherence.
- After the computerized assessment is completed, the CARE+ Corrections tool will provide tailored feedback based on their responses to the above questions.

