    - Statistics on OD upon release
    - Steps to preventing overdose
      - seeking treatment
      - make a plan to stay clean
    - Education about opiate, tolerance and purity, and danger of mixing opiates with other drugs/alcohol
    - Signs of overdose
    - How to respond to an overdose:
      - chest noogies
      - call 911
      - rescue breathing
      - Narcan
      - rescue position

The RA will then review the post-release/follow-up study procedures with the study participant, which includes collection of locator information, description of the post-release visit (see below), and explanation of continued follow-up.

Participants recruited inside the facility will receive typical discharge planning services as determined by the staff at the facility. For example, typical discharge planning for the DOC includes:

- 30 day supply of HIV medications (if patient is prescribed HIV medications)
- Appointment with community provider at Unity Health Care (contracted provider within the DC Jail) or referral to another community HIV provider
- DOC medical records

For participants in the intervention arm, recruited in the community, study staff will provide a cell phone and training on the text messaging portion of the intervention (described below).

At this visit, a post-release/follow-up appointment will be made for all study participants. In addition, study participants will be given study materials that provide information on the study clinic location, 800-number to call and make an appointment. In addition, participants recruited inside the facility will be given a flier reminding them to check in with the study staff upon release (See Appendix G).

Participants recruited in the community will receive a $50 incentive for completion of the baseline visit. Participants recruited in the correctional facility will receive their $50 incentive at the post-release follow-up visit (see below).

- Medical Chart Review: With subjects’ prior consent to the release of their medical records (see Appendix K: Medical Records Release Form) as included in the Informed Consent Form (Appendix D), relevant data will be collected from correctional facility and community provider medical records. Specific measures that will be abstracted include data from the 12 months prior to study enrollment related to HIV clinical care, comorbidities and sexually transmitted infections, and ancillary services (see Appendix I: Medical Records Abstraction Form).

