The longitudinal nature of the study (containing a baseline assessment before intervention and two follow-up visits after jail release) will result in repeated assessments of primary outcomes (plasma viral load suppression at Visits 2 and 3) and secondary outcomes (e.g., proportion linking to community HIV care at 30 days, 60 days, 90 days, etc.). These outcomes will be analyzed in the unified framework of generalized linear models (GLMs) with appropriate link functions (logit for dichotomized outcomes, e.g. linkage to care, detectable PVL; identify link for continuous outcomes, e.g. log-transformed PVL; or log link for count outcomes, e.g. # of non-main sexual partners). The setup of GLMs involves relating the expected outcome to a linear function of explanatory covariates, where the explanatory covariates will include a dummy variable encoding the treatment (=1) versus control (=0), dummies for study site and gender, relevant demographic covariates, and their interactions. Depending on the analysis objectives, three GLM model structures will potentially be used: 1) *Marginal models* will be used to analyze population-level intervention effect. Within-individual correlation of repeated measures will be accounted for using Generalized Estimating Equations (GEE),^6,7^ which yields consistent parameter estimates and robust standard error estimates. 2) *Random-effect generalized linear models* will be used to estimate the intervention effect at the individual-level.^8^ For those outcomes with only one follow-up visit, the model will be estimated using conditional logistic regression for binary outcomes or difference-on-difference regression for continuous outcomes for better estimation efficiencies. 3) *Markov transition models* will be used to investigate the intervention effect on the individual behavior change as previously conducted by this group,^9^ and includes the prior history of the outcomes as regression covariates; therefore, the transition model emphasizes more the effect of the intervention on outcome changes given the prior value of the outcome. Using these model setups, we will examine the different aspects of intervention for SA2 and SA3. These models will also allow us to quantify the differences between the two study sites and differences between male and female by testing the interaction between study arm and site, and potentially the interaction between study arm and gender.

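### For jail recruits, the viral load, CD4 count and part of the interview labelled baseline are collected after randomisation and the study session, contrary to the Analysis Plan's description

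*Protocol*

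**What the plan says.** The Protocol's Specific aim section defines the experimental arm as "CARE+ Corrections plus the community-based cell phone/text messaging intervention", so the counselling session is part of what is randomised.

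Under Baseline visit 2 the Protocol states: "Study participants will be randomized at this point to either the 1) intervention arm or 2) the control arm". It continues: "At the beginning of this visit with the participant, the RA will administer either the intervention (CARE+ Corrections tool) or the control condition". The blood draw described in that section is for community recruits only.

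For jail recruits the draw appears under Post-release visit, which is to be arranged within 14 days of release: "A blood draw will be conducted to provide a baseline measurement of plasma viral load and CD4 count". The same section describes the text messages as "reinforcing the prevention plan from the CARE+ Corrections session completed in jail prior to release", which confirms that counselling has already taken place.

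Baseline visit 1 splits the interview for jail recruits. The DOC Baseline CAPI is done in the facility and the Community Baseline CAPI at the post-release visit. If facility time is short, "some of these sections may be administered during the post-release community visit".

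The Analysis Plan summarises the design as "containing a baseline assessment before intervention and two follow-up visits after jail release". It compares baseline characteristics between arms to check the randomisation and adjusts for those found imbalanced. It offers a transition model with earlier outcome values as covariates, and it builds missingness weights on baseline covariates.

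**The concern.** A baseline value is useful because the assigned arm cannot have influenced it. A value taken after assignment and after half of the intervention does not have that guarantee. If the session shifts it, conditioning on it takes part of the intervention's effect out of the estimate. A difference between arms could also be read as chance imbalance and adjusted away.

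These values exist only for jail recruits who attend after release. Loss at re-entry is the problem the trial addresses, so the measures are absent for people whom the missing-data strategy most needs to describe. Attendance could also differ by arm, because the intervention arm receives its phone at that visit. That is an inference and not something the Protocol states.

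Finally, one label covers two things. For community recruits, baseline viral load comes from the visit at which they are randomised. For jail recruits it comes after the rest of their custody plus the time to the post-release visit.

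**Working it through.** The documents give no figure to reproduce, because the point concerns the order of events. The check traces that order and then asks where the values enter the analysis.

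**Order of events by recruitment setting**

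| Step | Jail recruits | Community recruits |
|---|---|---|
| Interview | DOC Baseline CAPI in the facility; Community Baseline CAPI and any deferred sections at the post-release visit | Combined Baseline CAPI at enrolment |
| Randomisation | Baseline visit 2, in the facility | Baseline visit 2 |
| Counselling or control video | Start of baseline visit 2 | Start of baseline visit 2 |
| Viral load and CD4 draw | Post-release visit | Baseline visit 2 |
| Text messaging (intervention arm) | Begins at the post-release visit | Phone and training at baseline visit 2 |

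For jail recruits, the gap from randomisation to the draw is the remaining time in custody plus up to 14 days as planned. The Protocol sets no limit on the time in custody, so the gap has no stated upper bound.

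For community recruits, the Protocol describes the draw before randomisation but places the session at the start of the same visit. The order within that visit is therefore also unclear, although both fall in one visit.

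**Where the values enter the analysis**

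1. *Marginal GEE model for suppression at Visits 2 and 3.* The covariates named are arm, site, gender, demographic variables and interactions. Baseline viral load is not among them, so the timing of the draw does not bias this comparison unless that variable is added.
2. *Transition model.* Earlier outcome values are covariates. For the first transition (baseline to Visit 2), the prior state is post-counselling in jail recruits. The second transition (Visit 2 to Visit 3) conditions on a post-randomisation value by design and raises no labelling problem.
3. *Randomisation check and adjustment.* The characteristics listed include sexual behaviours and drug and alcohol use. Both are interview domains and both are covered in the counselling session. If they fall in the part collected after release, a post-randomisation difference enters the check and may trigger adjustment. The allocation of domains to each part of the interview is in an appendix that is not available.
4. *Missingness weights.* These condition on baseline covariates without naming them. Any covariate collected only at the post-release visit is missing for those who did not attend.

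**Direction of the bias where it arises**

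Let a be the effect of the session on the post-release value and b the slope of the later outcome on that value. In a linear model with no other common cause of the two, adjustment estimates the total effect minus a × b. The loss is zero if either term is zero, and it is attenuation if both are positive. The Protocol gives neither a nor b.

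**Number without a baseline viral load (illustration only)**

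The Protocol allows up to 150 participants but gives neither the jail share nor the expected attendance. Assume half are jail recruits: 150 × 0.5 = 75. Assume 10% to 50% miss the post-release visit: 75 × 0.10 = 7.5 and 75 × 0.50 = 37.5, or about 8 to 38 people. This counts missing values and does not measure bias.

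**The case against.** The strongest reply is that the main comparison does not need baseline viral load. The marginal model compares arms at Visits 2 and 3, and its stated covariates do not include it. This stands. A reader might infer that the primary suppression result is biased as planned, but the documents do not support that.

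A reader might also infer that difference-on-difference would subtract any early effect from the primary outcome. The Analysis Plan limits that method to continuous outcomes with a single follow-up visit. Suppression is binary and measured at two, so the inference fails.

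Viral load and CD4 are not named in the list of baseline characteristics or among the weighting variables, and the transition model is only one of three structures that may be used. This also stands, and it makes the harm conditional.

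Any early effect on viral load may be small. Typical DOC discharge planning in both arms includes a 30-day supply of prescribed HIV medication, which would cover a draw made within 14 days of release. Text messaging begins only at that visit, and the draw might precede it, although the order within the visit is not fixed. This is a reason not to presume a large effect, but it does not turn the value into a baseline one.

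The DOC Baseline CAPI can precede assignment, so the Analysis Plan sentence is true of part of the baseline. It remains untrue of viral load, the variable behind the primary outcome.

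The choice of baseline value for each model could be left to a statistical analysis plan. Here, however, the Protocol itself fixes the visit order, applies the label and misstates the sequence.

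**Conclusion.** The point holds as a contradiction within the Protocol. In jail recruits, the viral load and CD4 draw, the Community Baseline CAPI and any deferred sections are post-randomisation data under a baseline label, and they are absent for those who do not attend after release. This follows from the visit schedule and needs no outside assumption.

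The statistical consequence is conditional. Bias can arise in the first step of the transition model, in adjustment for apparent imbalance and in the missingness weights, to the extent that these values are used there. The size cannot be derived from the documents, because the early effect of the session, its link to the later outcome, the jail share and post-release attendance are all unstated.

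**What to change.** - Define baseline as data obtained before randomisation.
- For jail recruits, classify the post-release draw and interview as post-randomisation data. Keep them out of the randomisation check, covariate adjustment, baseline prior-state terms and missingness weights. They can still be reported as early post-randomisation measures.
- Where a baseline viral load is needed for jail recruits, use the last chart value before randomisation. The planned chart review already covers "data from the 12 months prior to study enrollment related to HIV clinical care". Record the age of the value, and include a missing indicator and an indicator of recruitment setting. Confirm that the abstraction form captures the result and its date. The Re-incarceration Plan sets a precedent by accepting a chart viral load in place of a study draw, though only within two weeks of the visit.
- Correct the design sentence in the Analysis Plan and reconcile it with Baseline visit 1, Baseline visit 2 and Post-release visit. State the order of draw, assignment and session for community recruits too.

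The cost is wording and a data definition, with no new study visit or blood draw. The drawback is that some chart values will be old or absent, and they are not fully comparable with the fresh draw in community recruits. Moving more of the interview into the jail would also help, but it is an operational change that facility limits may prevent, and the fix does not depend on it.
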